### Cost effectiveness analysis

A sub-study evaluating cost effectiveness from an institutional perspective will be conducted to help inform total program costs, as well as the proportion of program costs linked to initial treatment vs. treatment of relapse for both the MAM and SAM trials. Cost per child treated, cost per child cured, costs per child who sustains recovery, and costs per child who fails to sustain recovery will be calculated for each study arm.

An activity and ingredients-based approach will be used to estimate total program costs. Cost data will be collected from accountancy records and through key informant interviews. Time allocation interviews will be conducted to determine personnel costs, apportion shared costs to project activities, and to exclude research costs. Program cost data will be adjusted for inflation and capital cost depreciation and assigned to the MAM and SAM studies. To differentiate between initial and relapse treatment costs, a per-visit cost will be calculated. This cost will then be multiplied by the length of stay to determine the average cost per child for initial and relapse treatment episodes. These costs, in turn, will then be multiplied by the number of children treated and relapsed, to estimate the total cost of initial vs. relapse treatment, respectively. Sensitivity analyses will be conducted where necessary to determine how uncertainty in costs and outcomes might affect cost-efficiency and cost-effectiveness estimates.

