### Intervention trials 1 and 2 follow-up visits during treatment

Children will be reassessed at health posts and health centers during follow-up visits every 7 days (SAM trial) or every 14 days (MAM trial) for up to 16 weeks after the time of enrollment, the maximum length of stay prescribed in the Ethiopian national guidelines. At each follow-up visit, a full set of anthropometric measurements will be reassessed, recent infectious symptoms (vomiting, diarrhea, fever, cough) will be queried of the caregiver, and appropriate appetite verified.

Children who appear to be progressing towards recovery will receive additional allotments of their assigned intervention. Children who are not progressing well (e.g., poor weight gain, feeding or health concerns expressed by their caregivers, poor clinical appearance including medical complications, etc.) will be either re-engaged in nutritional and health counseling, including the importance of full adherence to the allocated intervention, or referred to a higher level of care. Clinical assessments for complications will be completed similar to enrollment.

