• Experimental group A: Active Follow-up. In addition to the interventions received by the control group, caregivers will be requested to revisit the health post/center for scheduled follow-up visits at 4,12, and 24 weeks after recovery. If a caregiver fails to attend the scheduled health post/center visit, then a HEW or study staff member travel to the child’s home to remind them to complete the scheduled follow-up visit the following week or directly collect the data at the home as a last resort. This group is considered to have the most “active” follow-up procedures implemented by healthcare workers and volunteers.

• Experimental group B: Family MUAC Follow-up. In addition to the interventions received by the control group, caregivers will receive training on how to implement home-based MUAC and edema screening, including provision of MUAC tapes [41]. Caregivers will be educated how and when to assess their child’s MUAC and edema, and to return for care if their child’s MUAC falls into the AM category, their child has bilateral pitting edema, or at any time they are concerned about their child’s overall health. These children will also be scheduled for a single follow-up visit at 24 weeks after initial AM recovery.

Whenever a child in the post-recovery trial, regardless of study arm, is brought back to the health post, anthropometry will be assessed by study staff to determine whether or not the child relapsed to AM as well as to record overall growth trajectory. An additional health and demographics questionnaire will be completed. Those identified with AM will then receive treatment per the standard national protocol and continued to be followed for a total of 24 weeks from the time of initial recovery as some may relapse multiple times.

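### Total relapse cost multiplies a per-visit cost by a duration and by relapsed children; read literally, this omits repeat relapses and leaves the number of visits undefined

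*Protocol article*

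**What the plan says.** The section Cost effectiveness analysis sets out the calculation in three steps.

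- Unit cost: "To differentiate between initial and relapse treatment costs, a per-visit cost will be calculated".
- First multiplier: "This cost will then be multiplied by the length of stay to determine the average cost per child for initial and relapse treatment episodes".
- Second multiplier: "These costs, in turn, will then be multiplied by the number of children treated and relapsed". The results are the total costs of initial and of relapse treatment.

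Three other parts of the protocol article bear on this.

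- **Post-recovery – trial 3:** children found to have relapsed are treated under the national protocol and "continued to be followed for a total of 24 weeks from the time of initial recovery as some may relapse multiple times".
- **Intervention trials 1 and 2 follow-up visits during treatment:** visits take place "every 7 days (SAM trial) or every 14 days (MAM trial) for up to 16 weeks after the time of enrollment". The same sentence describes this 16-week limit as the longest length of stay in the national guidelines.
- **Post-recovery outcomes of interest:** relapse may be to severe (SAM) or moderate (MAM) acute malnutrition. The frequency of relapse and of return visits to the health post are both listed as outcomes.

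**The concern.** The units in the rule do not match.

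First, the last multiplier counts children, while the article expects some children to have several relapse episodes. A mean stay for one episode, multiplied by the number of relapsed children, charges each of them for one relapse only.

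Second, a cost per visit has to be multiplied by a number of visits. The rule multiplies it by length of stay, which the article uses elsewhere as a duration in weeks. The same duration corresponds to different numbers of visits when visits are 7 or 14 days apart.

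The sub-study is meant to report how programme cost divides between initial and relapse treatment, and the cost per child who does or does not sustain recovery, for each arm. The article itself says that SAM experimental group B may be more cost-effective but carries a risk of more relapse. If repeat relapse differs between arms, an undercount of repeat episodes does not cancel in the comparison, and it favours the arm with more of them.

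**Working it through.** The article gives no cost figure, so there is nothing to reproduce. The check compares the stated product with a direct sum over episodes. Rates of repeat relapse and the mix of SAM and MAM relapses are not given, so those below are assumptions.

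**1. Children versus episodes.** Let q be the number of further episodes per relapsed child, so that episodes per relapsed child are e = 1 + q. With a mean stay per episode:

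- stated total / true total = 1/e
- share of relapse cost missed = 1 − 1/e = q/(1 + q)

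| q (assumed) | e | share missed |
|---|---|---|
| 0.05 | 1.05 | 0.05/1.05 = 4.8% |
| 0.10 | 1.10 | 0.10/1.10 = 9.1% |
| 0.20 | 1.20 | 0.20/1.20 = 16.7% |

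**2. Simulated example.** Take 500 relapsed children with 1.21 episodes each, that is 605 episodes, and 3674 visits in all.

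- Mean visits per episode × children = (3674/605) × 500 = 3036, which is 17% too low.
- Mean visits per child, summed over that child's episodes, × children = (3674/500) × 500 = 3674, which is exact.

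The omission therefore depends on whether stay is averaged per episode or summed per child.

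**3. Effect on an arm comparison.** Suppose e = 1.1 in control and 1.3 in an experimental arm (assumed). The stated relapse-cost ratio, experimental to control, is then 1.1/1.3 = 0.85 of the true ratio, an understatement of about 15%.

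**4. Visits versus duration.** Visits = days of stay / interval. A 56-day stay is 56/7 = 8 visits on a 7-day schedule and 56/14 = 4 on a 14-day schedule. If the per-visit cost is multiplied by 8 weeks, the cost is right in the first case (8/8 = 1) and doubled in the second (8/4 = 2). If stay is counted in visits, this error does not arise. Using the 7- and 14-day intervals for relapse care is an assumption, because the article gives them only for the initial trials.

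**5. Net direction.** Assume stay in weeks, equal stays, one common per-visit cost and a share s of relapses to SAM. The stated/true ratio is then 1/[s + 0.5(1 − s)] divided by e. At e = 1.2 it runs from 2/1.2 = 1.67 (all MAM) to 1/1.2 = 0.83 (all SAM). The two problems pull in opposite directions.

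**The case against.** The strongest defence is that the wording can be read so that nothing is lost. The intermediate quantity is an average per child covering episodes in the plural. If it is summed over a child's episodes, multiplying by children is exact, as step 2 shows. Visits are also the natural unit to pair with a per-visit cost, and costs are assigned to the SAM and MAM studies separately. Finally, a journal article condenses a fuller protocol, where these details may be settled.

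Part of this stands. The benign reading is possible, so the article does not prove that relapse cost will be miscounted. But it is not how the article uses length of stay elsewhere, and nothing says that stay is counted in visits or summed over episodes. Nor is this just a detail left out: the article states the whole chain, including the multiplier. The planned sensitivity analyses address uncertain costs and outcomes, not the counting unit.

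A reader might go further and infer that a child who relapses to the other severity will be costed on the original trial's visit schedule, or that visits missed before a child is declared lost will be charged as delivered. The article makes neither choice. It gives intervals by trial for initial treatment, not by type of relapse, and it does not say when length of stay ends for a lost child. Neither inference is supported.

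**Conclusion.** The concern holds on the literal reading of the rule. Second and later relapse episodes drop out of the total, by about 5%, 9% or 17% of relapse cost at the assumed repeat rates of 5%, 10% and 20%. A per-visit cost is also applied to a duration whose relation to visits is not fixed. Both problems disappear if stay means visits, is summed over all of a child's episodes, and is paired with a visit cost that fits the care given.

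It would be too strong to say that relapse cost is certainly wrong, or wrong in a known direction. Every percentage here rests on an assumed repeat rate, interval or relapse mix. Only the cost sub-study is affected; the powered recovery comparison and its sample size are not. The change is still worth making, because the cost split and the cost per child by arm are what the sub-study is meant to deliver.

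**What to change.** In Cost effectiveness analysis, define treatment cost as a sum over every episode, initial and relapse: visits attended in that episode × a per-visit cost specific to the type of care given in it (SAM or MAM). Total this by randomised arm. Where a summary multiplier is kept for relapse cost, use the number of relapse episodes, not the number of relapsed children.

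The cost is a few sentences in the costing plan and slightly more data handling. Relapse frequency and return visits are already planned outcomes, so no new outcome is needed.

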## Discussion

The MODAM study encompasses three distinct, yet integrated, randomized controlled clinical trials evaluating the effectiveness of a number of novel interventions that have the potential to improve CMAM programs for the management of children with AM. The results will add to the context-specific body of knowledge available to guide policymakers in Ethiopia and other countries as they plan how to most efficiently implement and expand their national programs to address AM. Specifically, we anticipate providing new insights into the effectiveness of modified dosages of specially-formulated foods for both SAM and MAM, which are especially important considering the widespread adoption of some novel dosing schedules in many settings without a strong body of evidence.

In addition to the modified dosing strategies proposed, the MODAM trial has at least three significant design strengths that have not often been used in previous modified dosage studies. We believe these strengths may generate robust, compelling evidence that would provide new perspectives for policymakers before implementing modified dosage protocols. First is that we will prospectively provide different treatments and disaggregate results for children with SAM from MAM, as children with SAM have been seen to have less successful outcomes compared to those with MAM with these modified approaches [43]. While treating all children with AM in a unified program with a unified dosing regimen is certainly appealing, this runs the risk of being an *over*simplification due to the higher vulnerability of children with SAM. Second is that the individual participant randomization design, which we anticipate will provide a more robust level of evidence compared to cluster randomization used in prior studies in Ethiopia [44, 45]. In addition to baseline differences among the communities found in different clusters, cluster randomized trials are vulnerable to incorrect analytical methods, insufficient sample size, and improper analysis using the individual rather than the cluster as the unit of analysis [46, 47]. Third is that we will aim for a significantly smaller non-inferiority margin, with an associated larger sample size than most prior modified dosage studies, which we hope will provide more subtle information to stakeholders regarding both primary and secondary outcomes.

Only a small body of evidence exists regarding the experimental dosing regimens being tested for SAM treatment. There remains equipoise in terms of the interventions’ effectiveness, given the lower quantity of RUTF that most children will receive and some experience showing higher rates of stunting following discharge; however, the potential for significant cost savings, increased coverage, and simplification for frontline health workers may make these modified dosing schedules a worthwhile pursuit nonetheless. We hope that the development of cost-efficiency models incorporating the data generated by these trials will help provide policymakers with the information they need to make fully informed decisions as they balance these conflicting imperatives.

The experimental dosing regimens we will investigate for children with MAM have not been previously studied as far as we are aware, and include one experimental arm putting to the test a new WHO recommendation that RUTF may be used instead of RUSF for MAM [5]. While it would seem rather obvious that RUTF would be just as effective as RUSF, given that RUTF has an even better mix of complete protein than RUSF, its lower micronutrient content and less energy per sachet makes its presumed effectiveness less than guaranteed. The third experimental arm for MAM takes quite a different approach from the previously tested regimens of *reduced* dosage, instead opting for an increased dosage using 2 sachets (1000 kcal) of RUTF daily. The hypothesis here is that, by significantly increasing the amount of treatment food consumed on a daily basis, the length of stay might be significantly shortened, thereby saving financial costs overall and also decreasing the morbidity burden these children suffer while acutely malnourished if they are able to recover quickly.

We also aim to provide evidence regarding the effectiveness of the Family MUAC approach for a targeted high-risk population (children who have recently recovered from AM) known to have a significantly elevated risk of development of AM [16, 29]. Given the limited resources available for Family MUAC and the inconsistency of its success in the early identification of children with AM, this targeted approach is an opportunity to focus health worker resources on those for whom the benefit may be highest. The experience these caregivers have with previous successful rehabilitation from AM for their children may also increase their motivation to follow through with the home-based AM screening and to bring their children back to health posts/centers more rapidly, as they have seen the life-saving effects of the AM treatment. As far as we are aware, this is the first prospective study of the Family MUAC focused on this post-AM population and may provide a novel path forward for an operationally practical and cost-effective implementation of Family MUAC programs.

CMAM programs in high-burden settings all over the world struggle from similar challenges related to insufficient coverage for both diagnosis and treatment of AM, unfortunately largely a function of limited financial resources. The MODAM study is designed to provide insights into how to overcome some of these issues in an operational setting by rigorously testing approaches that can help extend available supplies of therapeutic and supplementary foods to treat more children, simplify supply chains, and more readily identify children at high risk for AM at an earlier stage of illness.

An important, and potentially challenging, aspect of the MODAM study is that this will be one of the first CMAM studies to incorporate the new 2023 WHO guideline on AM recovery criteria, requiring *all* three criteria of edema, MUAC, and WLZ to meet recovery thresholds [5]. This new recommendation comes from an appropriate logic, in that this ensures that children who are deemed recovered are not immediately readmitted using a different anthropometric criterion, but does carry the risk of prolonged length of stay and a higher number of children who would be deemed “failures” to recover. Our experience here will thus help to provide some of the first evidence on the effect this new WHO recommendation has in practice.

We have aimed to enroll rather large sample sizes (800 children in each study arm) in order to provide a relatively small non-inferiority margin (6%) for the AM treatment trials. This is ambitious, given the challenging situation in Ethiopia recently in terms of conflict in many areas and the relatively low rates of AM in areas not already being served by other CMAM program evaluations. There is thus the distinct possibility we will not be able to enroll the full sample size desired before trial funding runs out and we may need to accept a smaller sample size or eliminate one experimental arm in a given trial in order to achieve the same non-inferiority margin. It is also possible that recent violent conflicts will spill over into study areas causing potential pauses in research operations. Nevertheless, we aim to anticipate these potential challenges through the study team’s close collaborations with the Federal Ministry of Health and UNICEF, to proactively monitor contextual factors and plan accordingly.

At the conclusion of each trial in the MODAM study, results will be disseminated as soon as possible to the Federal Ministry of Health in Ethiopia and surrounding regions through consultative workshops and other platforms, in addition to peer-reviewed publications. We will make every effort to help ministries of health with interpretation and appropriate contextualization and implementation of any significant findings into national protocols that will support maximal coverage of optimal care for acutely malnourished children. After publication, raw de-identified data will be made publicly available and efforts will be made to collaborate with other researchers on additional analyses not yet anticipated.

## Data Availability

No datasets were generated or analysed during the current study.

## Abbreviations

AM: Acute malnutrition
CMAM: Community-based management of acute malnutrition
COVID-19: Coronavirus disease 2019
DSMB: Data and safety monitoring board
HEW: Health extension worker
IYCF: Infant and young child feeding
LAZ: Length-for-age Z-score
MAM: Moderate acute malnutrition
MODAM: Modified Dosages for Acute Malnutrition study
MUAC: Mid-upper arm circumference
MUACZ: Mid-upper arm circumference-for-age Z-score
RUSF: Ready-to-use supplementary food
RUTF: Ready-to-use therapeutic food
SAM: Severe acute malnutrition
WASH: Water, sanitation, and hygiene
WHO: World Health Organization
WLZ: Weight-for-length Z-score
